## Abstract

**Background:**

In Hong Kong, one of six couples is affected by subfertility problems. Male infertility contributes to half of the infertility cases. In male infertility, there is no effective treatment for patients with idiopathic infertility/poor semen parameters. Recent meta-analysis results suggest that a traditional Chinese medicine (TCM) formula — Wuzi Yanzong pill — showed a curative effect on male fertility. However, the heterogeneity of the studies could not draw a definitive conclusion on the therapeutic effect of this formula. The aim of this study is to conduct a well-designed randomized controlled trial to investigate the effect of TCM formula Wuzi Yanzong pill on improving semen qualities in men with suboptimal parameters.

**Methods:**

This study is a double-blinded, randomized placebo-controlled trial conducted in a public hospital in Hong Kong. Participants will be randomized, using computer-generated random numbers, with a 1:1 ratio to either the Wuzi Yanzong pill formula group or the placebo group. Both groups will be administered the drugs for 12 weeks. Participants will have a total of four visits for their semen and blood assessments for a 6-month period, and we will follow up for another 6 months to record their conception outcome. The primary outcome is to compare the total motile sperm count, natural conception rate, and pregnancy outcome to those under placebo treatment. Secondary objectives are sperm functions and assisted reproductive technology outcome.

**Discussion:**

To date, there are no studies using the disclosed Wuzi Yanzong formula or double-blinded, randomized trials. The Wuzi Yanzong TCM formula may provide a good clinical solution for subfertile males for which contemporary western medicine has no cure. Therefore, a well-designed randomized trial for evaluating the effect of Wuzi Yanzong TCM formula is urgently needed.

**Trial registration:**

Chinese Clinical Trial Registry (ChiCTR), ChiCTR-INR-17010790. Registered on 27 February 2017.

Centre for Clinical Research and Biostatistics - Clinical Trials Registry, CUHK_CCRB00548. Registered on 27 February 2017.

**Electronic supplementary material:**

The online version of this article (10.1186/s13063-019-3647-2) contains supplementary material, which is available to authorized users.

## Introduction

### Background and rationale

Subfertility is a common problem around the globe, affecting one in six couples in Hong Kong. Male infertility is responsible for half of the infertility cases in general. Infertility is defined as failure to conceive after 1 year of regular intercourse [1, 2]. Regarding semen quality, both sperm motility and concentration play important roles in achieving pregnancy. Among male infertile patients, there are less than 10% with congenital or genetic abnormalities and 20–30% with pathogenic statuses such as anti-sperm antigen, varicocele, or infection. The rest of the patients (30–50%) have idiopathic infertility (infertility for unknown reasons). This latter group of males presents with no adverse history affecting fertility and has normal anatomical and physiological structure and no endocrine or chromosome abnormalities. Among these males, more than 90% of their infertility cases are due to poor sperm motility, low sperm counts, or both [3].

For those idiopathic infertility males who do not satisfy World Health Organization (WHO) semen parameters, these parameters are categorized with different causes, but the two most important parameters are motility and concentration. Recently, there are reports showing that combining the two parameters as total motile sperm (TMS) count is a better predictive tool for male fertility [4, 5]. In contrast, there is no effective treatment for patients with idiopathic infertility/poor semen parameters.

In recent years, many new approaches have tried to delineate the etiology of idiopathic infertility, including using specific biomarkers, lifestyle analysis, body weight index, and “-omics” approaches, but the aim of developing a promising treatment remains unfulfilled. Testosterone replacement therapy once showed promise as an effective treatment for suboptimal semen quality even though few new testosterone formulations had been developed; however, the efficacies remain uncertain [6]. For this untreatable situation, using traditional Chinese medicine (TCM) may serve as an effective strategy to improve sperm quality in men with suboptimal semen parameters.

Wuzi Yanzong (WZYZ) is a traditional Chinese herbal formula with a long history firstly recorded in a Chinese medical book named Standards for Syndromes and Treatments, written by physician Wang Ken-tang of the Ming Dynasty (A.D. 1368–1644). This traditional Chinese herb formula was well documented in ancient Chinese medical books for its effectiveness. The formula consists of at least five herbs, but there are many variations. The original five-herb form included Fructus Lycii, Semen Cuscutae Chinensis, Fructus Schisandrae Chinensis, Semen Plantaginis, and Fructus Rubi, and this herbal formula has the therapeutic function of tonifying the kidney and supplementing the body essence. In Chinese medicine practice, it is commonly used to treat many kidney deficiency-associated medical conditions such as impotence, infertility, seminal emission, premature ejaculation, low back pain, and urinary incontinence. It has been shown that administration of WZYZ pills can significantly elevate the semen volume and sperm density in infertility patients with low semen counts [7, 8]. However, a large-scale and high-quality randomized placebo-controlled trial on the efficacy of WZYZ pills on semen quality and infertility has never been conducted. It is necessary to conduct a clinical trial to confirm whether WZYZ pills are efficacious in the treatment of patients with poor semen quality.

A recent meta-analysis showed that the WZYZ formula demonstrated a curative effect on male fertility. However, the heterogeneity of the studies did not allow one to draw a definitive conclusion on the therapeutic effect of this formula, mainly due to study problems such as small sample size, unknown randomization methods, bias in the placebo group, and a lack of details on the dosage of the herbal component used. There are no studies using a disclosed WZYZ formula and no double-blinded, randomized trials. An online database search revealed that a well-designed double-blinded, randomized clinical trial with a modest sample size is lacking. The WZYZ TCM formula may provide a good clinical solution for subfertile males for which contemporary western medicine has no cure. The rationale for conducting this randomized controlled trial (RCT) has been further discussed and published in our recent meta-analysis [9].

## Methods

### Aim

The aim of this study is to investigate the therapeutic effect of WZYZ pills on semen quality, sperm functions, and natural conception rate.

### Trial design and setting

This is a prospective, randomized, placebo-controlled, double-blinded, superiority trial with a 1:1 allocation ratio. It is conducted at Assisted Reproductive Technology Unit, Department of Obstetrics and Gynaecology, Faculty of Medicine, The Chinese University of Hong Kong. Our department conducted 892 semen analyses in 2017, in which 273 patients were diagnosed with oligoasthenospermia under the WHO criteria. The Standard Protocol Items: Recommendations for Interventional Trials (SPIRIT) checklist is provided as Additional file 4.

### Eligibility criteria

#### Inclusion criteria

Patients with less than 20 million total progressive motile sperm will be recruited in this study. Since the TMC is so far the most predictive indicator for achieving pregnancy [4, 5], other seminal parameters such as morphology and other physical properties are not included in the criteria.

#### Exclusion criteriaThe exclusion criteria for the study are as follows:

Male infertility due to one testicle being removed, history of undescended testis, previous chemotherapy, testicular torsion, or any other known abnormalities on reproductive organsPatients with azoospermia (indicating structural abnormalities or chromosomal abnormalities)Patients with known chromosomal abnormalitiesPatients with normal WHO (5^th^ edition) values for all parameters.

### Interventions

#### TCM WZYZ formula preparations

Traditionally and clinically most Chinese herbal medicines are prepared by decoction in boiling water for hours. In this study, the individual concentrated herbal medicine granules prepared from standardized decoction methods using state-of-the-art concentration technologies according to the Good Manufacturing Practices (GMP) standard will be obtained from PuraPharm® International (H.K.) Ltd. (Hong Kong). The individual concentrated herbal medicine granules will be prepared in sachet form. The modified Wuzi Yanzong pill will be composed of Fructus Lycii 2.4 g, Fructus Rubi 3 g, Semen Cuscutae Chinensis 2.4 g, Semen Plantaginis 2.4 g, and Fructus Schisandrae 2.4 g, plus Radix Rehmanniae Glutinosae Conquitae 3 g, Polygonati Rhizoma 3 g, Cistanches Deserticolae Herba 2 g, Epimedii Herba 2 g, and Cervi Cornus Colla 0.6 g, for a total of 23.2 g divided into two doses per day. For oral administration, the sachets at the designated daily dose are mixed to combine each Chinese medicine. A Certificate for Clinical Trial is not required, as our formula dose package has satisfied the Chinese Medicine Ordinance (Cap. 549 Laws of Hong Kong).

#### Placebo preparation

The placebo is produced by PurePharm International (H.K.) Ltd. with a newly established technology that can mimic the formula’s outlook, color and smell however without any active ingredients and thus no therapeutic effect. The placebo herbs are made indistinguishable in appearance and flavor from the treatment formula. The daily doses of the single form of the herb are packed in individual sachets for easy consumption under the GMP license. This new technology, on one hand, can prevent participants from recognizing being allocated to the placebo group, which could result in a lower compliance rate; on the other hand, it can prevent the potential beneficial effect from using vitamins or clomiphene as a placebo. Patients in the placebo group will consume the same amount of placebo herb as the treatment group.

#### Study process

A semen analysis will be performed for patients in our andrology unit. If the TMS count is less than 20 million per ejaculate, our reproductive medicine practitioner will exam the inclusion and exclusion criteria and consent the patient. After recruitment, the patients are assigned randomly by the TCM team and are divided into the control group taking the placebo and the treatment group taking the WZYZ formula twice a day regularly for a period of 3 months. Semen samples will be taken at the baseline (week 0) and at 6 weeks and 12 weeks to determine if the semen quality has been improved by the formula. An additional semen analysis will be performed 3 months after completion of the treatment. Natural conception and pregnancy outcome will be followed up by our clinical nurse for another 6 months. Compliance will be recorded in the patient diary and by the research nurse via weekly phone calls (90 days of treatment). Patients with less than 63 days of treatment intake will be excluded; the incomplete intake will be considered as failure of compliance too. If the total compliance is less than 70%, then the patient will be considered to have dropped out of the study. The flow chart and study schedule are shown in Fig. 1 and Table 1, respectively. Part of the semen sample will be cryopreserved and separately stored in a − 80 °C freezer for a DNA fragmentation test and other sperm function tests, which will be explained in the “Outcome measurements” sections. A blood sample will also be taken concurrently with the semen samples for hormonal level examination, including routine follicle-stimulating hormone (FSH) and free androgen concentrations.

**Fig. 1 Fig1:**
[figure not shown]
Study flow chart

**Table 1 Tab1:** Schedule of the study process

Time duration Time point	Study period								
	Recruitment by reproductive practitioner	Allocation by TCM team	Post allocation						
	1st visit	0 week	1–6 weeks	2nd visit^a^	7–12 weeks	3rd visit^a^	3–6 months	4th visit^a^	6–12 months
Enrollment:									
Eligibility screen	X								
Informed consent	X								
Allocation		X							
Interventions									
Administration of investigational product			X		X				
Assessments									
Semen analyses		X		X		X		X	
Blood tests		X				X			
Sperm DNA fragmentation		X		X		X		X	
Sperm cryotolerance		X		X		X		X	
Endocrine-disrupting chemicals test		X		X		X		X	
DNA maturity assay		X		X		X		X	
Liver and renal function assessment		X				X			
Natural conception and pregnancy outcome^b^									X

^a^ The 2nd through 4th visits are scheduled at the end of the time duration

^b^ Natural conception and pregnancy outcome are recorded by phone follow-up

#### Adherence

To enhance the validity of the data, multiple methods will be used to assess medication adherence, including the TCM package count and a phone call follow-up every week asking whether the participant takes the drug accordingly and reasons for non-compliance. Participants will return the unused drugs after 90 days. The unused drugs will be counted and recorded.

#### Concomitant care

The administration of other TCM supplements, as well as nutritional supplements for enhancing sperm parameters, are not permitted for all participants during the first 90 days, as these drugs/supplement may confound the effect of the TCM WZYZ formula.

### Outcome measurements

The primary outcome is to compare the TMS count, natural conception rate, pregnancy outcome, and live birth rate. Secondary objectives are sperm functions and assisted reproductive technology (ART) outcome as well as the safety assessment on the TCM formula.

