#### Semen analyses

A semen analysis will be performed using both manual analyses (by an andrologist) and computer-aided sperm analysis under WHO criteria. The clinical andrologist will have passed the quality assurance test (UK National External Quality Assessment Services [NEQAS]) to make sure he is up to standard. Semen parameters include volume, motility, viability, concentration, morphology, and total sperm count, and another physical status will be measured. A repeat semen analysis will be performed at 3 and 6 months after the treatment to assess the response duration.

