### Sample size calculation

Our andrology unit conducted 892 semen analyses in 2017, in which 273 patients were diagnosed with oligoasthenospermia, and the mean of the TMS count of all patients failed to fulfill WHO criteria (5th edition, < 20 million per ejaculate) is 8.08 ± 6.19 million TMS. To detect 100% (double the TMS) improvement by the WZYZ TCM formula and accepting a type I error of 0.05 and a type II error of 0.2, the number of subjects to be recruited into each arm to detect a significant difference is 115 on each arm (Medcalc®, Version 15.6.1). To allow for a dropout/non-compliance rate of 20%, the number of subjects required in each arm is therefore 181, and the total number of subjects required in the study is 286. Therefore, the whole recruitment takes approximately 12–18 months to finish.

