### Quality assurance

A Data Monitoring Committee (DMC) has been established. The DMC is composed of one independent chairman from the Clinical Research Management Office of the Chinese University, one independent member from the Department of Obstetrics and Gynaecology, and one independent member from the School of Chinese Medicine. The responsibilities of the DMC are data monitoring, interim analysis, assessing adverse events and cases with abnormal liver or renal function results after the intervention, reviewing core trial processes and documents, and discussing any amendments to the main study protocol.

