### Data analysis

All the data are reported as percentages for nominal data or means ± standard deviation (SD) for continuous data. Patients with less than 70% compliance (i.e., out of 90 days treatment taking the WZYZ formula, less than 63 days of treatment completed) will be excluded. They will be considered as having dropped out and will not be included in the final analysis, but will be included in the intention-totreat analysis. The compliance will be checked by our research staff based on the patient diary and phone calls every 2 weeks. For non-compliance and missing outcomes, we will use two sets of analyses. The full analysis set (FAS) will include all patients who are randomized and will be conducted according to the intention-to-treat principle. The per protocol set will include all patients of the FAS who complete follow-up and do not have serious protocol violations.

For the baseline comparison, the independent Student *t* test or the Mann-Whitney *U* test is used to evaluate the mean or median differences between the placebo and intervention groups for continuous data depending on whether the data are normally distributed, and the chi-squared test is used for frequency comparison. For longitudinal data with a baseline, we will use repeated measures analysis of covariance (ANCOVA) to evaluate the mean difference between and within groups. All the tests are two-tailed, and the significance level is defined as a value of < 0.05.

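### Four outcomes are called primary, all tests run at two-sided 0.05 and no success rule is stated, so neither the 5% error nor the 80% power describes the trial's primary conclusion

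*Protocol article*

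**What the plan says.** Outcome measurements puts four endpoints under one primary label: "The primary outcome is to compare the TMS count, natural conception rate, pregnancy outcome, and live birth rate". The abstract gives three and does not name live birth: "The primary outcome is to compare the total motile sperm count, natural conception rate, and pregnancy outcome to those under placebo treatment".

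Data analysis sets one threshold for everything: "All the tests are two-tailed, and the significance level is defined as a value of < 0.05". The article does not say whether one positive outcome is enough, whether all are needed, or whether they are tested in an order.

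Sample size calculation concerns TMS only: "To detect 100% (double the TMS) improvement by the WZYZ TCM formula", "accepting a type I error of 0.05 and a type II error of 0.2". It gives no control rate, target difference or power for conception, pregnancy or live birth.

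**The concern.** A type I error of 5% and a power of 80% describe a decision rule. With several outcomes called primary and no rule linking them, there is no single decision for those figures to describe.

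- **If any one outcome suffices**, testing each at 0.05 gives the trial more than a 5% chance of a false primary success.
- **If all are required**, the error rate is safe, but power for the joint criterion cannot exceed that of the weakest outcome, and three of the four have no stated power.

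The practical risk is a split result, such as a conception difference at p = 0.04 with no TMS effect, or the reverse. The protocol text would not settle whether the trial had met its primary objective.

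**Working it through.** **Inputs.** Number of primary outcomes: 4 (Outcome measurements) or 3 (abstract). Threshold: 0.05 two-sided for each (Data analysis). Sizing: TMS mean 8.08, SD 6.19 million, a doubling as target, type II error 0.2, 115 per arm before dropout (Sample size calculation). Natural pregnancy, ongoing pregnancy and live birth are recorded in the same participants (Natural conceptions and pregnancy outcome), so each is a subset of the one before.

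**The plan's own figure.** The article states no familywise error, so there is none to reproduce. The TMS sample size does not reproduce: 2 × (1.96 + 0.84)² × 6.19² / 8.08² ≈ 9.2, so 10 per arm rather than 115. That is a separate matter. Here it is enough that TMS is the only outcome for which a sizing is given.

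**Any one outcome suffices, tests independent.** Familywise error = 1 − (1 − 0.05)^k.

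- k = 3: 1 − 0.95³ = 14.3%
- k = 4: 1 − 0.95⁴ = 18.5%

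The Bonferroni ceilings under any dependence are 3 × 0.05 = 15% and 4 × 0.05 = 20%.

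**Any one outcome suffices, pregnancy outcomes nested.** The independent figures are too high because the three pregnancy outcomes are stages of one pathway. A simulation under no treatment effect used 115 per arm and a two-sided 0.05 test on each outcome. The article gives none of these rates, so all are assumptions:

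- conception 10%, 20% or 30%;
- ongoing pregnancy in 85% and then live birth in 95% of those (0.85 × 0.95 = 81% of conceptions), or 70% and 90% (0.70 × 0.90 = 63%);
- TMS either unrelated to conception or associated with it.

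| Set of primary outcomes | Independent | Nested (range over scenarios) |
|---|---|---|
| Four (main text) | 18.5% | 12.0–14.1% |
| Three (abstract) | 14.3% | about 11.5–13% |

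In every scenario the error is more than twice 5%.

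**All outcomes must succeed.** The chance of a false overall success is then at most 5%. Power satisfies P(all succeed) ≤ the smallest single-outcome power. The 80% planned for TMS would carry over only if the other three were certain to succeed whenever TMS did.

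To show how far the unstated part matters, these are powers at 115 per arm for assumed conception rates (two-proportion test):

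| Control v treated | Power |
|---|---|
| 5% v 10% | 30% |
| 10% v 20% | 57% |
| 15% v 30% | 78% |
| 20% v 40% | 92% |

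The range is too wide to call the trial underpowered or adequately powered for conception. The supportable statement is that the power is not given.

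**The case against.** The strongest reply is that a statistical analysis plan may exist and may contain a multiplicity rule. That stands for methodological detail. But the choice of primary outcome belongs in the protocol, and this article is not silent: it lists four outcomes and fixes 0.05 for all tests. A later hierarchy or alpha split would have to depart from that text.

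Several stronger readings are tempting and are not supported:

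- **That the false-positive risk is 14–19%.** This needs independent tests and an any-one-wins rule. The article states no such rule, and the pregnancy outcomes are nested, so 18.5% is an upper value.
- **That abstract and main text plainly contradict each other.** The article's own heading on pregnancy outcome covers live birth, so the abstract may simply be condensing. The wording should be aligned, but the point does not depend on it.
- **That interim testing inflates the error further.** The article says only "The responsibilities of the DMC are data monitoring, interim analysis". It states no efficacy test, timing or stopping rule, and such rules are commonly left to a charter.
- **That three post-baseline visits and two reading methods multiply the error.** The planned analysis of longitudinal data is one repeated-measures ANCOVA, and the article ties the post-treatment samples to duration of response. It does say semen is read by "both manual analyses (by an andrologist) and computer-aided sperm analysis", but not that each reading is tested separately.
- **That the trial is underpowered for conception.** This depends wholly on assumed rates. For example, 5% v 15% gives 81% power at 143 per arm (half of the stated total of 286).

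It is also fair to say that making TMS the primary outcome is one valid choice. A Bonferroni split (0.05 / 4 = 0.0125 each) or an explicit all-must-succeed rule would control the error too.

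**Conclusion.** The point holds in a limited form. Four outcomes (three in the abstract) are primary, all tests use two-sided 0.05, no success rule is given and only TMS is sized.

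If any one outcome counts, the familywise error is about 11–14% under the assumed nested rates rather than 5%; the independent-test values of 14.3% and 18.5% mark the upper end. If all must succeed, the error is controlled, but the 80% power does not apply to the trial's success criterion. Which of the two applies cannot be determined from the article, and that is the defect. For conception, pregnancy and live birth, power is unstated, not shown to be low.

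This should be corrected before unblinding, because it determines what the trial may claim.

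**What to change.** 1. Name one primary outcome: TMS at the end of treatment (week 12), estimated as the between-group contrast at that visit from the planned repeated-measures ANCOVA and tested at two-sided 0.05. TMS is the natural candidate because it is the only outcome sized.
2. Name in advance the one reading method, manual or computer-aided, that supplies the primary value. The article does not show which method lies behind the 8.08 ± 6.19 figure, so the sponsor must state it.
3. Make natural conception, ongoing pregnancy and live birth key secondary outcomes, tested in that order at 0.05 only if TMS is significant, each only if the one before it succeeds. Otherwise report them as estimates with confidence intervals. This fixed sequence keeps the familywise error at 5% without splitting alpha.
4. Align the abstract, the main text and the registry entries before unblinding.

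**Cost.** No additional patients or measurements. The pregnancy outcomes lose primary status, and no confirmatory claim can be made on them if TMS is not significant. Recruitment began on 27/02/2018, so this changes a registered trial's primary outcomes after it started. It must be a dated amendment that gives its reason and confirms that it was made without sight of unblinded data.
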